### B. Statistical Considerations

| SAS 8.2 (SAS Institute Inc., NC, USA) will be used for statistical analyses. All safety and adverse event data will be summarized separately for each group. The statistical analysis of the data will follow a standard intention to treat analysis. Changes in glucose and insulin concentrations, weight, body mass index (kg/m2), waist circumference, calculated FFM and FM and dietary intake will be evaluated. We will test overall time effects, treatment effects, and time*treatment interactions using ANOVA, and compare the changes in outcome measures between the groups using Student t-tests (if necessary after normalization of the outcome variable, or using the Wilcoxon Rank Sum test). First analyses will be conducted separately for changes between 0 and 4 weeks and for changes between 0 and 8 weeks. If similar results are obtained, the change between 0 weeks and the average of 4 and 8 weeks can be tested to reduce random within person variation. We will also conduct a data analysis stratifying by habitual coffee consumption before the start of the trial (i.e. 1-2 cups, 2-4 cups and >4 cups per day).  A goal of this pilot study is to obtain information on differences in outcome measures and variation to be used in a power analysis for a ‘definite’ trial which will be proposed in a future R01. The available data is insufficient to conduct a power analysis for effects of coffee on the outcome measures at this point, but previous dietary intervention studies of smaller size and shorter duration have been able to detect effects on parameters of glucose metabolism (43). |
| --- |

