#### B3. DESCRIPTION OF RESEARCH PROTOCOL

##### A. Study Design

| For this pilot trial we will use an 8-week randomized intervention study comparing the effects of caffeinated coffee (n=15), decaffeinated coffee (n=15), and no coffee (n=15) consumption (see figure).  the study medications. The 8-week intervention will be preceded by a 2-week run-in phase with no coffee consumption. At the initial visit, the 4 week visit, and the 8 week visit an oral glucose tolerance test (OGTT) will be conducted and measures of body fatness will be assessed. At the 6-week visit a nonfasting blood sample will be obtained to measure caffeine concentrations. Although we recognize the potential advantages of a cross-over study, the compliance to the interventions is uncertain and a cross-over design is particularly sensitive to decreases in compliance over time. The intervention will be blinded to the investigators. The intervention will be double blind with regard to the coffee type that participants receive (caffeinated and decaffeinated); we will ask the participants about whether they notice the type of coffee they receive.  **Screening** **Initial visit** **4 wk visit 6 wk visit** **8 wk visit**   | Run-in-phase (2 weeks)  (No coffee) | - Caffeinated coffee (n=15) - Decaffeinated coffee (n=15) - No coffee (n=15) | | --- | --- |   **Randomization:**  Randomization will be conducted by a statistician that is not involved in the study using blocking and stratification by sex to avoid differences in the proportion of men and women between the three intervention groups (35).  **Interventions:**  Participants in the intervention groups will consume 5 cups of instant caffeinated or decaffeinated coffee. The instant coffee will be provided in prepackaged plastic cups each containing the same amount of coffee that should be used to prepare one cup of coffee by adding hot water and 5 of these plastic cups are included in 1 bag (supply for 1 day). The 1-cup packages will not provide any clues whether they contain caffeinated or decaffeinated coffee. We will instruct participants on how to prepare the coffee, and ask them to consume a cup with every meal, and at mid-morning and mid-afternoon. Participants will be allowed to adjust the amount of added water according to their preferred coffee strength, but coffee should be consumed without caloric sweeteners. Artificial sweetener will be supplied to participants that prefer sweetened coffee. Participants who are randomized to the control (no coffee) intervention will be instructed to consume 5 cups of water. Before the start of the run-in phase, participants will receive dietary advice from a nutritionist to avoid coffee-related and caffeine-containing foods and drinks other than the coffee that will be provided. They will also be instructed to maintain a stable usual diet (including supplement use and alcohol consumption), and stable physical activity patterns throughout the study. In addition, participants are not allowed to use caffeine-containing medications such as certain flu remedies and analgesics or medications that may interact with caffeine including bronchodilators, quinolone antibiotics, monoamine oxidase inhibitors, anxiolytics, ranitidine, corticosteroids, growth hormone, and antihypertensives. To reduce symptoms related to caffeine withdrawal, we will instruct participants to gradually reduce their coffee consumption at the start of the run-in period and after completion of the trial over three days. We will provide extra coffee to the participants to allow this gradual reduction after completion of the trial.  **Visits**  Visits will be arranged as outpatient visits to the GCRC and none of the visits will not require an overnight stay.  1. Screening visit (1 visit)  The screening visit consists of:   - Signing the informed consent - An interview: medical history, medication use, use of drugs and alcohol, habitual physical activity - A physical examination including measurement of weight and height - An electrocardiogram, a urine HCG pregnancy test (women only), and drawing of fasting blood for blood glucose, liver function tests (AST, ALT, alkaline phosphatase), creatinine, and complete blood count (CBC).   2. Consultation nutritionist and run-in period  Subjects will meet with the nutritionist to receive instructions to avoid coffee-related and caffeine-containing food (other than the coffee provided) during the entire study. They will also be instructed to maintain a stable usual diet, and stable physical activity patterns throughout the study. To document adherence with the diet, subjects will be asked to record the type of foods and the food portions eaten for two weekdays and one weekend day for the week before the post-run-in phase visit and the visits 4 and 8 weeks later. Following this consultation, subjects will enter the 2-week run-in phase, which will serve as a washout period for the effects of previous coffee/caffeine use.  3. Post run-in phase and efficacy assessment visits (three visits)  These visits will occur immediately after the run-in-phase and 4 and 8 weeks after that. During these visits we will:   - Measure weight and waist circumference - Assess body composition using bioelectrical impedance analysis. - Measure systolic and diastolic blood pressure. - Collect fasting blood samples and conduct an oral glucose tolerance test drawing blood at 30 min, 60 min, and 120 min after the oral glucose load. Blood samples will be used to measure glucose, insulin concentrations, and lipid profile (LDL, HDL, and total cholesterol, triglycerides) and will be stored for possible future measurement of intermediary factors (e.g. adipokines). - Supply coffee sachets to the participants and provide instructions on how to prepare the coffee ( post run-in phase visit and week 4 visit only) - Count what is left of the provided coffee sachets to assess compliance (week 4 and week 8 visit only). Subjects will be invited to provide their ideas regarding possibilities to improve compliance. - Collect the 3-day dietary records and diaries in which participants will document deviations from the intervention protocol.   4. Visit with nonfasting blood draw (one visit)  This visits will occur in the afternoon 6 weeks after the run-in-phase. During this visit we will measure weight and systolic and diastolic blood pressure and collect a nonfasting blood sample. This sample will be used to measure s**erum caffeine concentrations to assess compliance.**  **Consistency of the provided coffee**  We will obtain instant coffee that is from the same batch to reduce variation in coffee characteristics. Also, we will store the product under optimal conditions (e.g. closed containers) and we will measure the amount of caffeine in caffeinated and decaffeinated coffee samples obtained at the start (that will be frozen) and at the end of the study.  **Technology employed in the study**  Demographic data and medical history: obtained by using a standardized questionnaire.  Anthropometry: Body weight, height and waist circumference will be measured according to standard protocols. The body mass index (BMI) is calculated as the weight (kg) over height2 (meters squared). Body composition will also be assessed by bioelectrical impedance analysis, using a single frequency bioimpedance analyzer (model 101, RJL Systems, Mt. Clemens, MI), and fat-free mass (FFM) and fat mass (FM) will be calculated (36). This method has previously been validated by comparison with DEXA measured FM (r=0.91) (37).  Dietary data: Using 3-day dietary records (2 weekday and 1 weekend day) we will calculate total energy intake, the number and distribution of meals and snacks, macro-and micronutrient intakes, and consumption of foods and drinks (particularly carbonated beverages and dairy using the Nutritionist Five program (First Data Bank, San Bruno, CA).  Assessment of blood pressure: blood pressure will be measured using multiple repeated measured with automatic Dinamap blood pressure meters using measurements after the participants has been seated for at least 5 minutes.  Oral glucose tolerance test (OGTT): An OGTT will be conducted in the morning starting before 10 am. Subjects will be instructed not to eat or drink after 8 pm not to use coffee after 5 pm on the preceding day. The glucose load will consist of 75 g glucose anhydrate in 300 ml of water ingested over the course of 5 min. An intravenous catheter will be placed in the forearm and blood samples will be collected before the oral glucose load (fasting), after 30 min, 60 min, and 120 min.  Laboratory data: Insulin will be measured using ELISA without cross-reactivity for pro-insulin, glucose will be measured using a photometric method. Fasting triglycerides and lipoprotein profile will be measured in a certified clinical lipid lab using standard methods (38,39). **Serum caffeine concentrations will be measured (using HPLC) in nonfasting blood samples obtained at the 6-week visit and in the coffee samples. B**lood samples will be stored for future determination of other possible intermediary effects of coffee using other funding sources.  Assessment glucose tolerance and insulin resistance: We will use the glucose area under the curve and 2-hr glucose as measures of glucose tolerance. Higher coffee consumption was associated with lower 2-hr glucose concentrations during an oral glucose tolerance test in several cross-sectional studies (5,29). We will calculate the ratio between the 30 min increment in insulin to 30 min increment in glucose concentration as a measure of early insulin secretion (40). We will calculate the homeostasis model assessment of insulin resistance calculated using the following formula: insulin resistance = fasting insulin x glucose / 22.5 (41). In addition, we will calculate the composite insulin sensitivity index (CISI) using the formula {10,000/the square root of [(fasting glucose x fasting insulin) x (mean glucose x mean insulin)]} during the oral glucose tolerance test. This measure has been shown in validation studies to provide a reasonably good measure of insulin resistance (42). |

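### Arms are compared on change from week 0 with no baseline covariate: a valid analysis, but generally less precise than a baseline-adjusted model, and one ANOVA test is diluted if week 0 is a time level

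*Protocol*

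**What the plan says.** Section B3, part B (Statistical Considerations) names two analyses. The first will "compare the changes in outcome measures between the groups using Student t-tests", if necessary after normalization or with a Wilcoxon rank sum test. The time windows are fixed: "First analyses will be conducted separately for changes between 0 and 4 weeks and for changes between 0 and 8 weeks". If the two windows agree, "the change between 0 weeks and the average of 4 and 8 weeks can be tested to reduce random within person variation". The second is an ANOVA: "We will test overall time effects, treatment effects, and time*treatment interactions using ANOVA". The text does not say which visits are its time levels. Neither analysis names the week-0 value or sex as a covariate.

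Section B3, part A (Study Design) shows that both are available. On the week-0 value: "At the initial visit, the 4 week visit, and the 8 week visit an oral glucose tolerance test (OGTT) will be conducted", with body measures at the same visits. On sex, randomization is done "using blocking and stratification by sex to avoid differences in the proportion of men and women between the three intervention groups". The arms are "caffeinated coffee (n=15), decaffeinated coffee (n=15), and no coffee (n=15) consumption".

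Part B gives no effect size, SD, between-visit correlation or power, and says the data are insufficient for a power analysis. It also says that the differences and variation observed in this pilot will feed the power analysis of a later trial.

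**The concern.** A change score uses the week-0 value with a fixed slope of 1. When the baseline carries within-person noise, as a single glucose-tolerance value may, the best slope is below 1. Subtracting the whole baseline then adds noise to the arm comparison. In any one trial it also over-corrects a chance baseline difference, which is easily large with 15 per arm. Each two-arm t-test estimates its error from 30 people (28 df), where one three-arm model with a baseline slope has 41 df.

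The ANOVA raises a separate question. If week 0 is one of its time levels, the treatment main effect averages in a visit that precedes treatment, so a real effect appears diluted.

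Two things are at stake. Section B1 makes the effect on weight, postload glucose and insulin sensitivity the second specific aim, and it is to be estimated from 45 people. The variance estimates are also meant to size the definitive trial. If that trial were sized on change-score SDs alone, the inefficiency would carry over.

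**Working it through.** **Inputs.** From the protocol: 15 per arm, three arms, visits at weeks 0, 4 and 8. Assumed, because the protocol gives none of these: equal variance σ² at each visit, equal correlation ρ between visits, two-sided 5% level. There is no stated power figure to reproduce.

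**1. One follow-up visit.** Per-subject variance:
- change score: 2σ²(1 − ρ)
- baseline-adjusted (ANCOVA): σ²(1 − ρ²)
- ratio: (1 + ρ)/2

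Estimating the slope costs a factor 1 + 1/(N − g − 2). With N = 45 and g = 3 arms this is 1 + 1/40 = 1.025. With N = 30 and g = 2 it is 1 + 1/26 = 1.038.

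| ρ | Ratio (1+ρ)/2 | Large-sample saving | Net saving, three-arm model | Net saving, pairwise ANCOVA |
|---|---|---|---|---|
| 0.4 | 0.70 | 30% | 28% | 27% |
| 0.6 | 0.80 | 20% | 18% | 17% |
| 0.8 | 0.90 | 10% | 8% | 6% |
| 0.95 | 0.975 | 2.5% | 0% | −1% |
| 0.99 | 0.995 | 0.5% | −2% | −3% |

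A simulation of the pairwise case (8,000 replicates) gave savings of 28%, 18% and 7% at ρ = 0.4, 0.6 and 0.8.

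The difference detectable with 80% power, in cross-sectional SD units, for the change t-test (28 df) against the three-arm ANCOVA (41 df) is 1.16 vs 0.97 at ρ = 0.4, 0.95 vs 0.85 at 0.6, 0.67 vs 0.64 at 0.8, and 0.34 vs 0.33 at 0.95.

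**2. The optional average of weeks 4 and 8.** Per-subject variance:
- change to the average: 1.5σ²(1 − ρ)
- ANCOVA on the average: σ²[(1 + ρ)/2 − ρ²] = σ²(1 − ρ)(1 + 2ρ)/2
- ratio: (1 + 2ρ)/3, which is 0.60, 0.73 and 0.87 at ρ = 0.4, 0.6 and 0.8 (large-sample savings of 40%, 27% and 13%)

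**3. ANOVA treatment main effect, if weeks 0, 4 and 8 are all time levels.** A constant effect τ appears as (0 + τ + τ)/3 = (2/3)τ. The mean of three visits has variance σ²(1 + 2ρ)/3. Rescaled to τ, this is (9/4) × σ²(1 + 2ρ)/3 = 0.75σ²(1 + 2ρ), or 1.35, 1.65 and 1.95σ² at ρ = 0.4, 0.6 and 0.8. ANCOVA on the averaged follow-up has 0.54, 0.44 and 0.26σ².

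**4. Power for illustration.** Take a difference of 0.8 SD at weeks 4 and 8 in one arm. This size is assumed. Values are from the noncentral t or F. The F noncentralities are 15 × (2/3) × (2τ/3)² / [(1 + 2ρ)/3] for the main effect and 15 × (4/9)τ²/(1 − ρ) for the interaction, with τ in SD units.

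| Test | ρ = 0.5 | ρ = 0.6 | ρ = 0.7 |
|---|---|---|---|
| Change t-test, week 8 | 0.56 | 0.66 | 0.78 |
| ANCOVA, week 8 (three-arm) | 0.68 | 0.75 | 0.84 |
| Change t-test, average of weeks 4 and 8 | 0.69 | 0.78 | 0.88 |
| ANCOVA, average of weeks 4 and 8 (three-arm) | 0.85 | 0.89 | 0.94 |
| ANOVA time-by-treatment interaction (4 df) | 0.61 | 0.72 | 0.85 |
| ANOVA treatment main effect with week 0 | 0.41 | 0.38 | 0.35 |

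The main effect has the least power, and it loses power as the correlation rises. The interaction does not share this fault.

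**The case against.** The planned t-tests are valid under randomization, and the trial is a feasibility pilot that makes no power claim. That stands and limits the severity.

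A reader might infer that the plan simply wastes 10% to 30% of the variance. The documents do not support that. The figure is (1 − ρ)/2 for ρ from 0.8 down to 0.4, the protocol states no correlation, and the figure leaves out the cost of estimating the slope. Nor does it carry over to every outcome. Weight, BMI and waist may track so closely over 8 weeks that adjustment gains nothing, although this too is an assumption.

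The plan also has a precision step of its own. The averaged change has slightly more power than ANCOVA at week 8 alone (0.69 vs 0.68 at ρ = 0.5), so setting only the single-visit t-test against ANCOVA would be unfair. Compared like with like, on the average, ANCOVA still leads (0.85 vs 0.69), and the averaging is optional and depends on the two windows agreeing.

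It might also be inferred that the whole ANOVA is a poor test. The interaction is the ordinary repeated-measures test of differential change, and in the illustration it has more power than the single-visit change t-test. The dilution of the main effect depends on week 0 being a time level. That is a natural reading of a test of overall time effects, but it is not stated, and a separate analysis plan could settle it.

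Calling the analysed changes raw would be too strong, since normalization and a rank test are allowed.

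None of this removes the core. The between-arm method is written into the protocol, it names no baseline covariate, and the covariate is already collected.

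**Conclusion.** The point holds as a gain in precision, of minor to moderate weight. With equal variances and a between-visit correlation of 0.4 to 0.8, one baseline-adjusted three-arm model would cut the variance of a single-visit arm contrast by about 28% to 8%, net of the slope cost. At 0.95 or more the gain is about nil. On the average of weeks 4 and 8, the large-sample variance ratio against the change score is (1 + 2ρ)/3.

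The ANOVA treatment main effect should not serve as the test of treatment if week 0 is among its time levels, because it then shows two thirds of a constant effect. The time-by-treatment interaction is not open to this criticism.

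A reader might go further and infer that the planned comparisons are biased. They are not: under randomization the change-score contrast is unbiased, and only its precision is in question.

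**What to change.** In section B3, part B, replace the t-tests on change and the ANOVA by one linear model per outcome:

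- Response: the week-4 and week-8 values as repeated measures.
- Terms: arm, visit, arm-by-visit, the week-0 value, and sex as the stratification factor.
- Covariance: unstructured within person.
- Estimates: the pairwise arm differences with 95% confidence intervals at week 4, at week 8 and averaged over both, all from this model.
- Scale: log-transform skewed insulin-based indices.

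Report the residual SD and the baseline-to-follow-up correlation for each outcome, so that the definitive trial can be sized for a baseline-adjusted analysis. If the ANOVA is kept as a secondary display, state which visits are its time levels, and do not use its treatment main effect as the test of treatment if week 0 is one of them.

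The cost is a change of wording. No visit, sample or measurement is added.

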### C. Subject Selection

| Overweight adult men and women will be recruited from the Boston community through advertisement and postings without regard for racial, social, economic, or other status.  *Inclusion criteria:*   1. Aged at least 18 years with an ability and willingness to give written informed consent. 2. Body mass index 25-35 kg/m2 3. Users of at least 2 cups of caffeinated coffee per day who are willing to be randomized to any of the interventions. 4. Non-smoking   *Exclusion criteria:*   1. Any condition/illness that may affect the study outcomes or would make participation potentially harmful such as pregnancy or breastfeeding, diabetes mellitus, heart disease, stroke, hypertension, malabsorption syndromes, GERD, a history of ulcer, according to a detailed medical history. 2. Abnormal hepatic function (liver function test > twice the normal range), abnormal renal function (creatinine > 1.1 mg/dl), fasting plasma glucose in the diabetic range (>/= 126 mg/dl), or blood pressure > 140/90 mmHg. 3. Present alcoholism or drug abuse or use of medications that could interfere with the treatment including bronchodilators, quinolone antibiotics, monoamine oxidase inhibitors, anxiolytics, ranitidine, corticosteroids, growth hormone, antihypertensives. These conditions will be screened for by a detailed history and systems review. |
| --- |

#### B4. POSSIBLE BENEFITS

| Subjects will receive a free screening, body composition and evaluation of glucose metabolism. It is hoped that the information from this study eventually will contribute to preventive efforts with regard to risk of type 2 diabetes. |
| --- |

#### B5. POSSIBLE RISKS AND ANALYSIS OF RISK/BENEFIT RATIO

| Risks to the subjects will be minimal, including slight pain, or bruise at the site of venipuncture. Potential side effects of the coffee use and caffeine withdrawal will be monitored closely. Caffeine abstinence can lead to withdrawal symptoms in regular caffeine users including headaches, fatigue, decreased energy/ activeness, decreased alertness, drowsiness, decreased contentedness, depressed mood, difficulty concentrating, irritability, being foggy/not clearheaded, flu-like symptoms, nausea/vomiting, and muscle pain/stiffness (44). Typically, symptoms of caffeine withdrawal have a peak intensity after 1-2 days and have a duration of 2-9 days (44). Increases in homocysteine concentrations (45) and blood pressure (average increase: 1.2 mmHg for systolic and 0.5 mmHg for diastolic blood pressure) (46) have been reported as a results of (caffeinated) coffee consumption and systolic and diastolic blood pressure will be measured at each visit. If any serious side effects of the interventions are detected, participants will be withdrawn from the study protocol.  Risk protection / prevention procedures  We will ask the subjects to stay in close communication with us in case any symptoms that could possibly be attributed to the study. One of the investigators will carry a pager at all times for 24 hour per day access by subjects. Confidentiality will be maintained through our computer‑based data coding system. Results obtained from individual subjects will be analyzed, reported and discussed in reference to the subjects code. The principal investigator will maintain complete control over all data. If there appears to be good reason to share information with other investigators this will be done only by reference to the subject's entry code. |
| --- |

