#### B6. RECRUITMENT AND CONSENT PROCEDURES

| Recruitment Strategy  We plan to enroll ~45 subjects over 4 weeks. To achieve this, we will need to screen approximately 20-25 subjects per week at the GCRC (to have 1 subject meeting the study eligibility criteria out of approximately 2 subjects screened). We expect that the number of persons that has to visit the hospital for screening will be relatively low because the eligibility criteria are not very restrictive and can to a large extent be assessed through a preceding telephone interview. We will recruit from the Boston community through advertisements and posters. We have extensive experience with recruiting and screening subjects and have previously used successfully the techniques we propose to use herein. Thus, we do not feel that enrolling the number of patients needed would pose any problems.  Consent procedures  The purpose of the study, the risks involved, reimbursements for study related costs, and the importance of the subject's full cooperation will be explained to each subject and will also be included in the consent document, which each subject will read and sign before entering the study. Details of the protocol will be explained to subjects and written informed consent will be obtained. The subjects also will be informed that they may withdraw from the study at any time. Constant medical supervision will be provided throughout the study period. A copy of the protocol and the consent form will be given to each patient and a copy of the consent form will be archived. |
| --- |

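### Section B5's withdrawal rule, read naturally, ends all remaining visits after a serious side effect, so outcomes that the intention-to-treat analysis needs are never measured

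*Protocol*

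**What the plan says.** The rule is in Protocol section B5, on risks: "If any serious side effects of the interventions are detected, participants will be withdrawn from the study protocol". Section B6 separately covers voluntary exit: "The subjects also will be informed that they may withdraw from the study at any time". Neither section says whether a person who stops is measured again.

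Section B3.A (Study Design) sets the assessments: "At the initial visit, the 4 week visit, and the 8 week visit an oral glucose tolerance test (OGTT) will be conducted". The same three visits include the instruction "Measure weight and waist circumference", together with body composition and blood pressure, and the week-4 and week-8 visits include the sachet count. A further visit at week 6 measures weight and blood pressure and takes the blood sample for serum caffeine, which serves the adherence aim in section B1.

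Section B3.B (Statistical Considerations) fixes the analysis: "The statistical analysis of the data will follow a standard intention to treat analysis". The comparisons are of changes: "First analyses will be conducted separately for changes between 0 and 4 weeks and for changes between 0 and 8 weeks". If the two sets of results are similar, "the change between 0 weeks and the average of 4 and 8 weeks can be tested to reduce random within person variation".

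**The concern.** An intention-to-treat comparison works best when outcomes are measured in everyone randomized, whether or not they still take the assigned drink. A conduct rule that ends the visits when the drink ends works against this. It removes week-4 or week-8 measurements from people selected because they had a side effect of the intervention, so the missing values cannot be assumed to be like those that remain.

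This belongs in the protocol. A statistical analysis plan can say how missing values are handled, but it cannot create a glucose tolerance test that was never done. Staff have to decide when the event happens whether to book the next visit, and the B5 sentence either tells them not to or leaves the matter open.

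The adherence aim is touched as well. Someone who stops because of a side effect is informative about adherence, and the week-6 caffeine sample and the sachet counts take place at the visits that would be lost.

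**Working it through.** The protocol gives no event rate, dropout rate or standard deviation, so there is no stated figure to reproduce. The check is of the text first, then of scale.

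**1. Scope of the rule.** B5 withdraws the person from the study's protocol as a whole, and B3.A makes the visits part of that protocol. Where B3.A means the regimen alone it uses a narrower term, in the diary item: "Collect the 3-day dietary records and diaries in which participants will document deviations from the intervention protocol". The wider term in B5 therefore most naturally covers the visits too. This is an inference. The narrower term appears once and is not defined, and B6 uses a third wording for full exit.

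**2. What is lost, by time of withdrawal** (visits from B3.A, contrasts from B3.B):

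| Withdrawn | 0–4 week change | Week-6 caffeine sample | 0–8 week change | Average of weeks 4 and 8 |
| --- | --- | --- | --- | --- |
| Before week 4 | lost | lost | lost | lost |
| Between weeks 4 and 6 | kept | lost | lost | lost |
| Between weeks 6 and 8 | kept | kept | lost | lost |

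**3. Bias in one arm.** Inputs: 15 per arm (B3.A); assumed 0 or 1 person lost from the arm; assumed difference D between the leaver's change and the mean change of those who stay, 0.5 to 1 SD of the change score. With fraction f lost:

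full-arm mean − mean of those who stay = f × D

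- Nobody lost: 0.
- One lost, D = 0.5: (1/15) × 0.5 = 0.033 SD.
- One lost, D = 1: (1/15) × 1 = 0.067 SD.

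If the person leaves after week 4, this applies to the 0–8 week contrast, and the bias in the 0–4 week contrast is 0. If both arms of a comparison lose one similar person, the two terms cancel.

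**4. Against sampling error**, in SD units:

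- Standard error, 15 v 15: √(2/15) = 0.365.
- Standard error, 14 v 15: √(1/14 + 1/15) = 0.372.
- Bias as a share of the standard error: 0.033/0.372 = 0.09 and 0.067/0.372 = 0.18.
- Loss of precision: 0.3716/0.3651 = 1.018, so the standard error rises by 1.8%.

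**5. Dilution if the person is kept.** Someone who stops at the start and from then on gains nothing from the drink lowers that arm's mean effect by 1/15 = 6.7%. For a stop after week 4, the 0–4 week change is not diluted, and the 0–8 week change is diluted by at most that amount.

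**The case against.** The strongest case against is that this is a preferred wording for one ambiguous safety sentence. B5 mentions neither visits nor data. Ending study procedures after a serious side effect, including a glucose tolerance test with a catheter in place, is a defensible cautious choice in a study whose risks are called minimal. The trigger may never occur in 45 habitual coffee drinkers, the size rests wholly on assumed inputs, and the trial is a feasibility pilot for which no power analysis was possible. Most of this stands, and it limits the point to a low priority. It does not remove it: the rule can keep its safety purpose without ending every measurement, and leaving its scope open still leaves staff to decide case by case.

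Two stronger readings are tempting, and the document supports neither.

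- *A reader might infer that B5 contradicts the intention-to-treat statement.* It does not. No text removes anyone from the analysis set. The rule affects which measurements exist, not who is analysed.
- *A reader might infer that the losses would fall mainly in the two coffee arms.* The rule applies to all three arms. B5 describes effects (homocysteine, and an average blood-pressure rise of 1.2/0.5 mmHg) only for caffeinated coffee, calls none of them serious, and names no risk specific to decaffeinated coffee. By the protocol's figures, a 3-day taper followed by up to 9 days of symptoms ends by about day 12 of the 14-day run-in. That suggests that caffeine withdrawal should usually be over before the intervention starts. It does not show that serious events will occur in either coffee arm.

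One practical objection also holds: someone who stops may go back to usual coffee or stay caffeine-free, and these give different later measurements. The fix has to record which.

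**Conclusion.** The point holds as a cheap improvement. On its natural reading, B5 ends the remaining week-4, week-6 and week-8 visits for anyone with a serious side effect of the intervention, and no measurement is planned afterwards. The loss is related to treatment because of its trigger, but its direction and the arm most affected are not established.

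Its size is 0 if nobody is withdrawn. For one person lost from an arm of 15 it is about 0.03 to 0.07 SD, well inside sampling error, with a negligible loss of precision. The figures rest on two assumptions that the protocol does not supply: the number withdrawn (0 or 1 per arm) and the leaver's difference from those who stay (0.5 to 1 SD). Confidence is moderate, because the scope of the sentence has to be inferred. No conclusion of this pilot is likely to change. The wording matters somewhat more if it is carried into the definitive trial.

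**What to change.** Replace the B5 sentence with wording such as:

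> *A participant with a serious side effect of the intervention will stop the assigned drink (with a gradual reduction if needed). Where safe and with consent, the participant still attends the remaining scheduled visits (weight and waist only if an OGTT is not advisable), records coffee and caffeine intake, and is analysed in the randomized arm.*

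The gradual reduction is named because B3.A provides one only at the start of the run-in and after the trial is completed. The right to leave altogether, in B6, is untouched.

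The cost is one sentence and at most three visits, already scheduled, per person who stops. Recovery will be partial, since some will decline and some should not have the glucose test. Keeping such people dilutes that arm's effect by up to about 7% per early stopper, which is inherent in the intention-to-treat analysis already chosen.
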